**Design:**

The study is a crossover randomised controlled trial. Participants will be recruited from inpatient and outpatient psychiatric treatment centres, on the approval of their treating physician. A healthy control group will be recruited using online advertising. All participants will undergo each of three conditions in randomised order: 20 min of cycle ergometry at 50–60% of maximum heart rate; 20 min of exercise at 70–80% of maximum heart rate; and 20 min of quiet reading. Immediately before and after each condition, participants will be asked to complete a computerised Stroop test, watch a film containing substance-related images and self-report craving levels. During the Stroop test and film viewing, participants’ neural activity will be measured via functional near-infrared spectroscopy.

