### Study design

This study is a randomised controlled trial involving three conditions: moderate exercise, intense exercise, and rest. Alcohol-dependent, cocaine-dependent and healthy control subjects will undergo all three conditions in randomised order. The order will be determined using a computer-generated ordering system. The random sequence was generated by the web-based Research Randomizer (randomizer.org), which yielded 60 permutations of the order of sessions (rest, moderate exercise, intense exercise). These permutations were printed, placed in separate envelopes and given to a colleague not involved in the study to distribute upon recruitment of each participant. Due to the nature of the intervention, blinding will not take place. The funder has no role in the design, analysis or interpretation of the study.

No data monitoring committee is involved in this study as the intervention (exercise) is not untested or high risk, and as only two acute sessions are involved any adverse events will be addressed immediately by the investigative team. The study therefore meets the criteria of “non-critical indications where patients are treated for a relatively short time and the drugs [in this case, exercise] under investigation are well characterized and known for not harming patients” [41].

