### Inhibitory control

For the assessment of inhibitory control, a computer-based version of the Stroop test is administered with E-Prime 2.0 (PST, USA). During the task, participants are presented with a colour word appearing in the same colour (e.g. “blue” printed in blue) on compatible trials or in a different colour (e.g. “blue” printed in green) on incompatible trials. While the word meaning has to be ignored, participants are instructed to press a key corresponding to the ink colour. The conflict resulting from the presentation of the relevant and irrelevant dimensions of the stimuli challenges the attentional system. In this respect, a system that efficiently suppresses task-irrelevant dimensions allows fewer conflicts between the colour word and the ink colour. This indicates greater efficiency of the inhibitory control system. Similar to the original Stroop paradigm, computerised versions of this task have been found to elicit interference effects and to have a high reliability [47].

In the present study, participants complete 12 practice trials, followed by four test blocks with 54 trials each. Sufficient practice rounds are included to reduce learning effects. In each test block, only compatible or incompatible trials are presented to allow the detection of interference effects using fNIRS. The blocks are alternated and the trial type employed in the first block is counterbalanced across participants. Between blocks there is a 30-s fixation period, which allows HbO_2_ concentrations to return to baseline. During each trial, the stimuli are presented over 2000 ms or until a response is collected. The inter-stimulus interval is varied randomly between 200 and 400 ms to avoid guessing.

The different colour words were presented with equal probability across all trials. For the assessment of task performance, the accuracy and reaction time (on response-correct trials) are calculated for incompatible trials.

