### Alcohol or cocaine cue exposure

Alcohol-dependent participants will be asked to report the type of alcohol (wine, beer, schnapps) which they chiefly consume or prefer. It has been established that, in research involving substance cues, craving is more reliably elicited by cues specific to the individual and their consumption history, and is consequently not a reaction to arousing cues in general [48]. Cocaine-dependent participants will not undergo this step, as there is no variation in the substance itself. All participants will be shown a block of six 1-min films, alternating cocaine cues or alcohol cues (of the preferred substance) with neutral cues. Neutral cues have to be included to be able to associate changes in HbO_2_ with craving rather than visual processing alone. Each 1-min film is separated from the next by a 30-s fixation period, which allows HbO_2_ concentrations to return to baseline. The same film block will be shown at every time point (specifically, prior to and after every condition, for each of the three conditions) in order to ensure that there is no variation in the emotional intensity of the cue.

Each 1-min film is designed to replicate activities carried out in a real-life setting. In order to achieve this, the films are created with a small camera strapped to the head, so that the viewer sees everything from the perspective on the camera holder and can see their hands picking up objects, etc. In the alcohol-cue films, the camera holder walks through a supermarket, arrives at the aisle selling the preferred beverage of the participants, looks at the bottles, picks some up and finally puts some in a basket before moving on. In the neutral films shown following the alcohol films, this sequence is repeated but some type of cleaning product is the examined and chosen. In the cocaine-cue films, the camera holder walks to a flat surface, takes out a small bag of cocaine and begins to snort it or prepares it in lines. The neutral cues are filmed in the same environment, but another activity (making tea, writing, opening a book) is undertaken on the flat surface.

Prior to the study start, the films will be tested on 10 alcohol-dependent and 10 cocaine-dependent individuals (who will not later take part in the study) in order to ensure that the film reliably elicits craving.

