### Experimental conditions

To estimate the maximal heart rate of each participant, the algorithm 211 – (0.64 × age) will be used [57].

All participants will undergo three conditions, on three separate days, in a counterbalanced order. The days on which participants participate will be separated by 2–4 days. All sessions will take place in the same laboratory room at the Department of Sport, Exercise and Health at the University of Basel. Trained members of the investigative team will oversee all conditions. Owing to the nature of the intervention, investigators will not be blinded to the conditions.

The reading condition serves as a resting state comparison. Subjects will be asked to read an article about architecture in Basel. The article is 13 pages long, excluding references.

The moderate exercise condition requires participants to train on a cycle ergometer at between 50 and 60% of their maximal heart rate. Participants will wear a heart rate monitor, which will be constantly observed by study personnel, to ensure that they exercise with the correct intensity. If the participant exceeds or fails to meet the appropriate intensity, prompts will be given. Prompts will not be recorded. This constitutes a moderate, aerobic exercise bout. The exercise will last 20 min.

The intensive exercise condition is identical to the moderate condition, but participants will exercise at a pulse of between 70 and 80% of their maximal heart rate, constituting a bout approximately at the anaerobic threshold.

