### Statistics

Sample size is calculated a priori using G*Power 3.1 [58]. Based on effect sizes reported in previous studies [25, 40] and an alpha level set to 0.05, the initial power analysis indicates that 17 participants per group are required to reach 85% statistical power. As drop-outs have to be expected, the sample size is increased to 20 participants per group. Note that the power analysis is based on the acute effects of moderate aerobic exercise on prefrontal cortex activity and inhibitory control. The statistical analysis of collected data is performed with SPSS 23.0 (IBM Statistics, USA) for Windows. Acute effects of exercise on inhibitory control and HbO_2_ concentration are examined using a 2 (group: alcohol dependent, healthy controls) × 3 (condition: control, moderate exercise, highly intense exercise) × 2 (time: pre, post) ANOVA on reaction time and the haemodynamic response to incompatible trials of the Stroop colour–word test. Additionally, effects of exercise on cue-elicited craving and HbO_2_ concentration (neutral cues subtracted from alcohol/cocaine cues) are investigated by applying a 2 (group) × 3 (condition) × 2 (time) ANOVA. Main effects and interactions are reported. Subsequently, Bonferroni-corrected *t* tests are used to decompose any significant interactions. The level of statistical significance is set to *p* < 0.05. Data from participants who do not complete all three measurement points will not be used.

Regarding missing data, as participants who do not complete all three sessions will be excluded from the study, it is anticipated that missing data will chiefly be due to faults in the fNIRS and Stroop programming, and thus will be missing at random. For this reason, multiple imputation will be used to address this issue.

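### The group × condition × time ANOVAs are valid under random order but lose precision: they omit session number and use the pre-session value as an outcome level, not as a covariate

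*Protocol article*

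**What the plan says.** The Statistics section names every factor of the model. Stroop reaction time and the haemodynamic response are analysed by group × "3 (condition: control, moderate exercise, highly intense exercise) × 2 (time: pre, post) ANOVA". Cue-elicited craving and its haemodynamic response are "investigated by applying a 2 (group) × 3 (condition) × 2 (time) ANOVA". Main effects and interactions are both to be reported. No session, period or sequence factor appears. The only covariate mentioned anywhere is perceived stress (General stress section), as a possibility, and it is not in the stated model.

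The measurements repeat within and across sessions. The abstract says "Immediately before and after each condition, participants will be asked to complete a computerised Stroop test", and the cue-exposure section says "The same film block will be shown at every time point (specifically, prior to and after every condition, for each of the three conditions". That makes 2 × 3 = 6 exposures to the same material.

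Learning is addressed in two ways. The Inhibitory control section says "Sufficient practice rounds are included to reduce learning effects", and the order of conditions is randomised. Study design reports a web randomiser that "yielded 60 permutations of the order of sessions (rest, moderate exercise, intense exercise". Experimental conditions says "All participants will undergo three conditions, on three separate days, in a counterbalanced order". Neither section describes blocking or stratification of orders by group.

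**The concern.** In a three-period crossover with repeated tasks, practice and cue habituation are expected. The Discussion itself, commenting on an earlier study, says that improvement over repeated measurements would be expected. A model without session cannot separate such an effect from the error.

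A pre/post factor tested through condition × time is also equivalent to analysing change scores. A change score gives the pre-session value a weight of exactly 1. That is the best weight only if, within a person, a session that starts one unit higher also ends one unit higher.

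What is at stake is precision. The study plans on 17 analysable participants per group, and two of its hypotheses for intense exercise predict no difference (self-reported craving and prefrontal response to cues). Wide intervals make such a result hard to interpret.

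**Working it through.** **The plan's own figure.** The article gives 17 per group for 85% power at alpha 0.05. This cannot be reproduced forward, because the effect size, test family, sidedness and repeated-measures correlation are not given. A corrected sample size therefore cannot be derived; what follows compares variances.

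**1. Weight on the pre-session value.** Assumed: unit SD at every measurement, pre-post correlation within a session rw, correlation between any two measurements in different sessions rb. For two conditions compared within one person:

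- Change-score contrast: variance = 4(1 − rw).
- Adjusted contrast: b = (rw − rb)/(1 − rb), variance = 2(1 − rb)(1 − b²).
- Since 1 − rw = (1 − rb)(1 − b), the ratio adjusted/planned is (1 + b)/2.

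With rw = 0.8 the planned variance is 4 × 0.2 = 0.80.

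| rb | b | adjusted variance | ratio | reduction |
|---|---|---|---|---|
| 0.8 | 0 | 0.40 | 0.50 | 50% |
| 0.6 | 0.50 | 0.60 | 0.75 | 25% |
| 0.4 | 0.67 | 0.667 | 0.83 | 17% |
| 0.2 | 0.75 | 0.70 | 0.875 | 12.5% |
| 0 | 0.80 | 0.72 | 0.90 | 10% |

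At b = 0.9 the reduction is only 5%. At b = 0.5, the precision that the planned contrast has with 17 participants needs 17 × 0.75 = 12.75, about 13.

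**2. What practice leaves in the condition × time contrast.** Let g1, g2, g3 be the average pre-to-post change due to repetition alone in sessions 1 to 3.

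- A shift common to pre and post of a session cancels in post minus pre.
- If g1 = g2 = g3, the change cancels between conditions.
- Otherwise, under random order, the contrast gains mean-zero noise with variance 2S² per person, where S² is the variance of the three g values (divisor 2).

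Illustration, on the scale of the within-person SD with b = 0.5 (planned variance 4 × 0.5 = 2): take a decelerating curve proportional to exp(−k/1.5) over exposures k = 0 to 5. A curve of size 2 gives g of about −0.97, −0.26 and −0.07, so S² = 0.228 and the inflation is 2 × 0.228/2, about 23%. Sizes 1 and 3 give about 6% and 51%. A linear curve gives 0%. None of these curves comes from the protocol.

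**3. Condition main effect.** This averages pre and post, so a session-level shift does not cancel there. The plan reports this effect too.

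**4. Validity and power by simulation** (n = 17, one group, random order, 1,500 runs per scenario). With no true effect, the largest mean estimate was 0.018 SD, within simulation error, and the planned test rejected in 3.5% to 5.9% of runs. Power at b = 0.5, for an effect that gives the planned contrast 85% without practice:

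| | no practice | decelerating, size 2 |
|---|---|---|
| planned contrast | 85% | 76% |
| + session | 83% | 82% |
| + pre-session covariate | 92% | 92% |
| + both | 91% | 90% |

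**5. Cost of the session term with no session effect.** Averaged over random orders, the contrast variance rises by about 6% at n = 20 and 7% at n = 17. At b = 0.5 and n = 20 the net ratio is 0.75 × 1.06 = 0.795, still about 20% below the planned contrast. Break-even is (1 + b)/2 × 1.06 = 1, so b is about 0.89.

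**6. Balance of orders.** Twenty participants cannot be divided evenly over six orders (20/6 = 3.33) or three positions (20/3 = 6.67). The chance that moderate exercise and rest differ by 5 or more first-session placements depends on how the list was made. With 60 independent random orders it is 22% in a given group and 52% in at least one of three. With ten of each order shuffled over the whole list it is 13% and 29%.

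**The case against.** The strongest reply is that a group × condition × time ANOVA is a standard and valid pre-post analysis, that order is randomised, and that practice trials are included. This stands as far as validity goes. A reader might infer from the missing session term that practice over all six exposures contaminates the exercise effect, or that false positives are inflated. Neither follows. Level shifts and equal gains cancel in the condition × time contrast, and what remains is noise around zero that the error term already reflects.

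It is also fair to say that the size of the gain is unknown. The 50% end needs a pre-session value with no session-specific information (b = 0), the gain shrinks toward nothing as b approaches 1, and the cost of omitting session runs from nothing to substantial depending on the practice curve.

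A reader might also infer that the orders are unbalanced. The article does not settle this: 60 is exactly ten of each order, and a balanced list is not excluded. What is missing is any statement that balance was sought within groups.

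The reply that such details belong in a separate analysis plan has less force, because the article states the factors of the model outright.

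**Conclusion.** The point holds as one of precision, not of bias. The stated ANOVAs leave out session and do not use the collected pre-session value as a covariate. The covariate is the larger and more dependable gain: 17% to 50% lower contrast variance if rw = 0.8 and rb = 0.4 to 0.8, and 10% to 12.5% if rb is 0 to 0.2. The correlations are assumptions. The session term helps only if the pre-to-post change differs between sessions, for example through a larger gain in session 1; otherwise it costs about 5–7%. Together the two terms beat the planned contrast unless b already exceeds roughly 0.87 to 0.90. For the condition main effect, session-level shifts do remain, so it should not be read as an exercise effect without a session term. It is a change worth making, but leaving it out would not invalidate the trial.

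**What to change.** Replace the ANOVAs with a mixed model for the post-session value containing condition, session number (1–3), group, group × condition, the pre-session value and a random participant effect. Split the pre-session value into the participant's mean over the three sessions and the session's deviation from it, so that the within-person coefficient b, which governs the condition contrasts, is not mixed with the between-person one. Take the exercise effects from the condition and group × condition terms of this model.

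The cost is a change of analysis wording and two degrees of freedom for session, with the variance penalty shown above if no session effect exists. No new data are needed.

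In addition, state how the 60 orders were generated and whether they were balanced within each group. If they were not, call the order randomised and not counterbalanced. As recruitment was incomplete when the article was written, any participants still to be enrolled could be given the six orders in blocks within group.

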### fNIRS recordings

Using fNIRS (NIRSport, NIRx Medizintechnik GmbH, Germany), cerebral oxygenation is recorded during the inhibitory control task and alcohol cue exposure. Probes are applied using a flexible cap adjustable to the participant’s head size. Light sources and detectors are placed over the prefrontal region using the Fz position of the EEG as reference. Channel distances are fixed to 35 mm to allow measurements at equal depths. Offline processing of the collected data is performed with Homer 2 [54] and includes the following steps: removal of discontinuities, artefact rejection and correction using spline interpolation, band-pass filtering (0.01–0.2 Hz), conversion into haemodynamic states using the modified Beer–Lambert Law [55] and normalisation using the pre-task period as baseline. As findings of a review have indicated widespread prefrontal cortex hypoactivation during inhibitory control tasks and hyperactivation during the presentation of drug-related cues, cerebral oxygenation is examined across channels placed over the prefrontal region [7].

HbO_2_ is calculated as the dependent variable, because Strangman et al. [56] have shown high correlations between this parameter and the blood oxygen level. For the assessment of cue-elicited craving, difference waveforms (created by subtracting the haemodynamic response to neutral cues from alcohol/cocaine cues) are extracted for statistical analysis.

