A final key issue that this study aims to shed further light on is the value of fNIRS assessments in addiction treatment. In the past 2 years, this technique has been used in the assessment of anxiety in heroin users [67], working memory in ecstasy users [68] and investigations of gambling [69] and Internet addiction [70]. While the simplicity, cost-effectiveness and lack of physical restrictiveness noted earlier are all attractive features of the device, it must be recognised that the bulk of the limbic system, which plays a crucial role in substance addiction [71], cannot be imaged using fNIRS. In order to maintain reasonable signal-to-noise ratios, only cortical brain activity (2–6 mm into cerebral tissue) can be mapped using fNIRS. Furthermore, recent research on the fNIRS methodology suggested that systemic changes in the extracerebral and intracerebral blood flow might compromise the interpretation of measured fNIRS signals (which is also true for other haemodynamic-based techniques such as fMRI) [72]. However, with a thorough experimental design and precise instructions to the study participant, these potential confounding factors can be kept to a minimum. Through its advantages especially in applications that require high ecological validity, and due to its high level of consistency with traditional neuroimaging techniques, fNIRS has a great potential to expand our knowledge on the functional organisation of the brain [73].

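### The Stroop analysis uses incompatible trials only and omits accuracy, so a non-specific exercise effect can be mistaken for a change in inhibitory control

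*Protocol article*

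**What the plan says.** Statistics examines acute effects on inhibitory control and HbO2 with a group × condition × time "ANOVA on reaction time and the haemodynamic response to incompatible trials" of the Stroop test. Compatible trials and accuracy are not named there.

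Inhibitory control describes the task as a conflict between word meaning and ink colour, with a more efficient system allowing fewer such conflicts. On the block structure it says: "In each test block, only compatible or incompatible trials are presented to allow the detection of interference effects using fNIRS". On scoring it says that "the accuracy and reaction time (on response-correct trials) are calculated for incompatible trials".

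The cue films are handled differently. Alcohol or cocaine cue exposure explains that "Neutral cues have to be included to be able to associate changes in" HbO2 with craving and not merely with visual processing. fNIRS recordings then states that "difference waveforms (created by subtracting the haemodynamic response to neutral cues from alcohol/cocaine cues) are extracted for statistical analysis", and Statistics repeats the subtraction.

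The Discussion acknowledges that "systemic changes in the extracerebral and intracerebral blood flow might compromise the interpretation of measured fNIRS signals", and adds that careful design and instructions can keep this to a minimum.

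**The concern.** The task section treats inhibitory control as resistance to interference and builds the blocks so that interference can be measured. The analysis then never forms the contrast between incompatible and compatible trials. Someone who responds faster to everything after cycling will be faster on incompatible trials even if interference is unchanged.

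The pre/post measurements and the reading session control for time and practice. They do not control for a general effect of exercise, because that effect appears in the exercise sessions from pre to post and is absent from the reading session. It is part of the condition × time interaction that the ANOVA tests.

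Inhibitory control and the haemodynamic response to the Stroop test are both listed as primary outcomes in the Abstract, and the Discussion calls the role of inhibitory control in craving a key aspect of the study. What is at stake is whether an observed change can be attributed to inhibition in particular.

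Accuracy is a second gap. Reaction time is taken from correct trials only, so faster but more error-prone responding would show as a gain unless accuracy is tested beside it.

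**Working it through.** **The plan's own figure.** Statistics gives 17 per group for 85% power at alpha 0.05, raised to 20 for drop-outs. The step to 20 is consistent with 15% loss: 17 / (1 − 0.15) = 20. The 17 cannot be reproduced, because the effect size, the test and the repeated-measures correlation are not stated. Solving backwards, 17 would need a paired standardised effect of 0.77 (two-sided), or a repeated-measures f of about 0.14 to 0.39 over 1–3 groups, 2–6 measurements and correlations of 0.5–0.7. The point does not depend on this figure, but it cannot be seen whether the power refers to incompatible trials or to interference.

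**What a general shift does to each measure.** Let g be the exercise-minus-rest change that acts on both trial types, and h the true change in interference.

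- Incompatible only: g + h.
- Incompatible minus compatible: (g + h) − g = h.

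This cancellation is exact for a constant shift in ms. For proportional speeding a remainder stays. With assumed times of 650 ms (compatible) and 750 ms (incompatible), 3% speeding gives 22.5 ms on incompatible and 19.5 ms on compatible trials. The contrast retains 22.5 − 19.5 = 3 ms.

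**How often it would be significant.** None of these inputs is in the document. Assumed: times as above, SD of the change contrast 40 or 60 ms, correlation 0.7 between trial types, n = 20, no change in inhibition beyond general speeding. A two-sided 5% paired t test on the exercise-minus-rest difference in pre-post change was simulated 20,000 times per setting. The contrast column spans constant and proportional speeding.

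| General speeding | Incompatible only, SD 40 | Incompatible only, SD 60 | Incompatible minus compatible |
|---|---|---|---|
| 2% (15 ms) | 36% | 18% | about 5–6% |
| 3% (22.5 ms) | 67% | 36% | about 5–7% |
| 5% (37.5 ms) | 98% | 75% | about 5–10% |

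The contrast stays near 5% when the speeding is constant and reaches about 10% only with proportional speeding of 5% and SD 40.

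**HbO2.** fNIRS recordings lists normalisation to the pre-task period and a 0.01–0.2 Hz band-pass filter, and the task has 30-s fixation periods between blocks. These largely remove a steady rise. They do not remove a systemic response evoked by doing the task itself. Compatible blocks, recorded in the same run, are the available reference for that part.

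**Cost in sensitivity.** With equal variances and correlation r, the variance of the difference relative to one measure is 2(1 − r): 1.0 at r = 0.5, 0.6 at r = 0.7, 0.4 at r = 0.8. Signal can shrink too. If compatible trials share half of the true gain (assumed), the standardised effect is multiplied by 0.5 / √(2(1 − r)):

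- r = 0.5: 0.50
- r = 0.7: 0.5 / √0.6 = 0.65
- r = 0.8: 0.5 / √0.4 = 0.79

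So the contrast can lose sensitivity even when r exceeds 0.5.

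**The case against.** The best defence is that the hypotheses are worded as behavioural performance on the Stroop test and prefrontal activity during it, not as interference. Incompatible-trial measures answer those questions as worded. This stands, and it is why the incompatible-only result should be kept. It does not cover the step in Statistics that labels the same analysis as one of inhibitory control.

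Four stronger readings are tempting, and the document does not support them.

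- **That raised blood flow after exercise will pass straight into the Stroop HbO2 result and be read as better inhibition.** Normalisation, filtering and fixation largely remove a steady shift. The hypotheses also list Stroop performance and prefrontal activity separately. Only task-evoked non-specific change remains at issue, and it would be read as prefrontal activity.
- **That performance is judged on reaction time alone.** Accuracy is calculated; it is only missing from the stated ANOVA.
- **That the bias favours the trial's hypotheses throughout.** For intense exercise the Background predicts reduced Stroop performance and reduced prefrontal activity. General speeding or a general HbO2 increase would work against those predictions. The full predicted pattern, better after moderate and worse after intense exercise, could not come from a non-specific gain that rises with intensity.
- **That the two Stroop outcomes support no conclusion.** They support one about Stroop performance; attribution to inhibition is what weakens.

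It may also be said that the handling of accuracy could sit in a fuller document. That may be so, but the article does fix which measures enter the ANOVA.

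**Conclusion.** The point holds as a defect of specificity. As written, the analysis cannot separate a change in inhibitory control from a non-specific exercise effect common to both trial types, although the data to do so are collected and the film analysis follows that logic. A speed-accuracy trade-off would also go undetected.

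The misattribution is possible, not certain, and its size depends on how much general speeding or task-evoked systemic change occurs, which the document does not give. The simulated range of about 18–98% false attribution at n = 20, against about 5–10% for the contrast, rests wholly on the assumed reaction times, SDs, correlation and 2–5% speeding. It illustrates the mechanism and does not estimate the risk in this trial. For the moderate-exercise comparison the error leans towards the hypothesis; for the intense-exercise comparison it leans away. The case for replacing the incompatible-only measure outright is weaker, since the stated power may rest on it.

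**What to change.** - Add compatibility (compatible, incompatible) as a within-person factor to the Stroop ANOVAs for reaction time and HbO2, giving group × condition × time × compatibility.
- Base any claim specific to inhibitory control, or to inhibition-related prefrontal activity, on the interaction of the exercise effect with compatibility. This is equivalent to analysing incompatible minus compatible, and matches the films.
- Keep the incompatible-only result, reported as Stroop performance.
- Run the same ANOVA on accuracy, and claim no improvement in performance if accuracy falls.

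The compatible blocks are already recorded, so no extra data collection is needed. Accuracy and correct-trial reaction time would also have to be scored for compatible trials. The cost is possible loss of sensitivity: the interference contrast is noisier when the correlation between trial types is low, and smaller when compatible trials share part of the true gain. The stated 85% power with 17 per group may not apply to it, and the plan should say so.
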